| Clinical Follow-up Visits/Testing | 
Subjects will be followed through two years post implant.
 
Required Testing
 
 
▪ Baseline evaluation: Informed consent, history and physical, pregnancy testing for women of childbearing age, 12-lead electrocardiogram (ECG), CHA2DS2-VASc score, HAS-BLED score, Modified Rankin Scale (mRS), medication assessment
 
▪ Procedure: Transoesophageal echocardiogram (TOE) or intracardiac echocardiogram (ICE) only when combined with baseline/pre-procedural TOE, angiogram, adverse event assessment
 
▪ Post procedure/Pre-Discharge: TTE, medication assessment, adverse event assessment
 
▪ 1M to 3M: TOE, medication assessment, adverse event assessment
 
▪ 6M (+/- 2 weeks): Phone contact follow-up for medication and AE assessment
 
▪ 12M (+/- 6 weeks): Medication and adverse event assessment
 
▪ 24M (+/- 12 weeks): Phone contact follow-up for medication and adverse event assessment
 
▪ Interim/unscheduled visits: per physician discretion
 
 |
| Suspected Stroke/TIA Evaluation   | 
 
▪ All subjects suspected of a stroke should be seen by a stroke/TIA neurologist for evaluation and appropriate neurological testing done (i.e. magnetic resonance imaging (MRI), computed tomography (CT))
 
▪ Modified Rankin Scale (Appendix J)
 
▪ TOE should be conducted to verify the presence of device-related thrombus
 
                                                                                                                                                                                                                                                                                                                                                                                                                                                                                                                                                                                                                                                                                                                                                    |

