**Table 3: Study visits and electronic case report forms (Appendix H)**

| eCRF                | Visit | Enrollment & Baseline | Procedure | Discharge | 1-3M | 6M Phone Visit | 12M | 24M Phone Visit | Interim Follow-up |
|---------------------|-------|-----------------------|-----------|-----------|------|----------------|-----|-----------------|-------------------|
| Baseline            |       | X                     |           |           |      |                |     |                 |                   |
| Inclusion/Exclusion |       | X                     |           |           |      |                |     |                 |                   |
| Procedure           |       |                       | X         |           |      |                |     |                 |                   |
| Follow Up           |       |                       |           | X         | X    | X              | X   | X               | X*                |
| Medication          |       | X                     | X         | X         | X    | X              | X   | X               | X                 |
| Protocol Deviation  |       | X**                   | X         | X         | X    | X              | X   | X               | X                 |

\*Complete if stroke or TIA is confirmed

\*\* Complete if informed consent/informed consent form was not appropriately obtained/completed, visit out of window, test not completed.

Additional eCRFs, reports and assessment noted below should be completed upon occurrence, and/or as applicable:

- Withdrawal eCRF
- Adverse Event eCRF
- Protocol Deviation eCRF
- Death eCRF
- Follow-up eCRF for interim/unscheduled visits
- Modified Rankin Scale (**Appendix J**) (complete 90 days after confirmed stroke /TIA)

If a suspected stroke/TIA has occurred, the subject should be seen by a stroke/TIA neurologist for evaluation and appropriate neurological testing (i.e. CT or MRI, and CTA or MRA). If a stroke or TIA is confirmed, a TOE is required as soon as possible to confirm device placement, LAA flow parameters and presence/absence of device-related thrombus. See Section 8.1 for further details.

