## **12. STATISTICAL METHODS**

No formal hypothesis will be tested for this observational post-market study. However, point estimates and exact 95% confidence intervals will be provided for the following rates in the study:

- Procedural serious adverse events (0 - 7 days) post procedure or before hospital discharge whichever latest) will be summarized for all subjects as well as stratified by imaging modality used for implanting the device (TOE and ICE)
- Late serious adverse events through 2 years
- Occurrence of ischemic stroke , systemic embolism and cardiovascular death through 2 years
- Occurrence of bleeding (including hemorrhagic stroke) events through 2 years

Data collected on the following objectives will also be reported:

- Technical success (secondary objective)
- Procedural success (secondary objective) - This objective will be summarized for all subjects as well as stratified by imaging modality used for placement of the device (TOE and ICE)
- OAC usage through 2 years (secondary objective)

- Serious Adverse Events – this may include, but is not limited to:
  - Significant bleeding events (e.g. cardiac tamponade, central nervous system (CNS) bleeding, and any bleeding related to the device or procedure that necessitates an operation)
  - Endocarditis
  - Device embolization (summarized by those that can be snared, and those that require surgical intervention)
  - Thrombus on device
  - All strokes
  - Transient ischemic attacks
  - Systemic embolism
  - Cardiovascular death
- Closure at procedure and 1-3 months post implant
  - The echo core lab's adjudication of residual flow will be used for this analysis. The following guidelines will be used:
    - None – No color flow jet in or out of the LAA
    - Small leak: < 3 mm diameter jet by color flow Doppler
    - Medium leak: 3-5 mm diameter by color flow Doppler
    - Large leak: > 5 mm diameter jet by color flow Doppler

Other variables may be summarized as deemed appropriate. The numerator for all rates will be the number of subjects who experience the corresponding event. The denominator for all rates will be subjects who experience the corresponding event plus all other subjects who achieve 2-years of follow-up.

Version 9.0 or higher of the SAS® statistical software package or other widely accepted statistical software will be used to provide all statistical analyses. Unless otherwise stated, attempts will not be made to adjust for multiple comparisons.

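### The 2-year-completer denominator for all rates does not suit closure, which is read from an image at the procedure and at 1-3 months

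*Protocol*

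**What the plan says.** Section 12 of the Protocol has two reporting lists. The first promises that "point estimates and exact 95% confidence intervals will be provided for the following rates in the study" and names four event outcomes. The second covers further data to be reported and includes "Closure at procedure and 1-3 months post implant". For closure, "The echo core lab's adjudication of residual flow will be used for this analysis", in four grades: none, small, medium and large.

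After both lists the section defines how rates are formed. "The numerator for all rates will be the number of subjects who experience the corresponding event", and "The denominator for all rates will be subjects who experience the corresponding event plus all other subjects who achieve 2-years of follow-up". Closure is not exempted. No image-based denominator appears in Section 12, in Section 13.3 on the core laboratory, or in the leak grading of Appendix E.

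**The concern.** A closure grade is fixed when the image is read. Whether the subject is still in the study at 24 months has no bearing on it. A denominator built on reaching 2 years has three effects on closure:

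- A completer with no readable image is in the denominator but cannot be in the numerator, and so counts as not closed.
- A subject with an imaged leak who exits before 2 years is in neither part of the closure rate. A subject with an imaged closure who exits equally early is in both. That leak is still counted in the rate for its own grade.
- Each grade has its own denominator (that grade plus the other completers), so four mutually exclusive categories share no common base.

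The reported closure percentage would then mix the image result with how complete the imaging was and with exits up to 2 years later.

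**Working it through.** **Can the problem cases arise?** The Synopsis requires "TOE, medication assessment, adverse event assessment" at 1-3 months. Missed tests are nevertheless foreseen: the notes to Table 3 give "visit out of window, test not completed" among the reasons for a Protocol Deviation form. The 24-month visit is "Phone contact follow-up for medication and adverse event assessment", so a subject can complete 2 years without ever having the 1-3 month image. Section 6.8 foresees death, withdrawal and loss to follow-up. The protocol states no rate for any of these and no expected closure rate, so there is no figure of its own to reproduce.

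**Formula.** Let c be the true share in a grade among readable images, p the share of subjects with a readable image, and r the 2-year retention. Assume exit is unrelated to grade or imaging. The numerator share is pc, and the other subjects contribute only if they complete:

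reported share = pc / [pc + (1 − pc)r]

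**Illustration at 1-3 months.** Assumed true grades are 90 / 5 / 3.5 / 1.5%, with r = 0.85.

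| Readable (p) | Closure under the rule | Sum of four grades |
|---|---|---|
| 100% | 0.900 / 0.985 = 91.4% | 103.1% |
| 95% | 0.855 / 0.978 = 87.4% | 98.5% |
| 85% | 0.765 / 0.965 = 79.3% | 89.2% |
| 70% | 0.630 / 0.945 = 66.7% | 74.9% |

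Varying r from 0.80 to 0.90 at p = 0.85 gives 80.3% to 78.3%. The extreme corners are 0.900 / 0.980 = 91.8% (p = 1, r = 0.80) and 0.630 / 0.963 = 65.4% (p = 0.70, r = 0.90). Against the true 90% these are errors of +1.8 and −24.6 points.

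**Cancellation.** Setting the reported share equal to c gives pc = cr / (1 − c + cr) = 0.765 / 0.865 = 0.884, so p is about 0.98. At that level of imaging the two errors offset in the closure figure. With fewer readable images the net error is downward.

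**Check with whole numbers and a different assumed truth (85% closed, 1000 implanted).**

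- All imaged, 800 completers, 200 exits (170 closed, 30 leaking): closure is 850 / (800 + 170) = 87.6%, against 850 / 1000 = 85.0%. Any leak is 150 / (800 + 30) = 18.1%. The two sum to 105.7%.
- 800 completers of whom 100 have no image, 200 exits of whom 100 were imaged (85 closed, 15 leaking): closure is 680 / (800 + 85) = 76.8%, against 680 / 800 = 85.0%. Any leak is 120 / (800 + 15) = 14.7%. The two sum to 91.6% (from unrounded values).
- No exit and no missing image: the rule returns 85% and the grades sum to 100%.

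With readable images as the denominator, closure is 85.0% in all three cases and the grades sum to 100%.

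**The case against.** The strongest reply concerns scope. Section 12 uses the word rates when it introduces the four event outcomes. Closure comes under a different lead-in, and a residual-flow grade of none is not naturally an event that a subject experiences. The authors may have meant the rule for events only, leaving the closure denominator to a statistical analysis plan that is not shown here. That reading is possible, but it is not what is written. The sentence follows both lists and covers all rates, and the second list also holds strokes, TIA and systemic embolism, to which a rate rule plainly applies. An analysis plan that used imaged subjects for closure would depart from the protocol's literal sentence.

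Several limits on importance and size stand:

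- A reader might infer that closure is the study's main evidence that the device works. Sections 4.3.1 and 4.3.2 do not support this: closure is in none of the four primary or three secondary objectives, and no confidence interval is promised for it.
- A reader might also conclude that the result could not be compared with published closure rates. The protocol gives no denominator for any such rate, so the point cannot rest on that.
- The larger downward errors depend on assuming that 15-30% of images are missing or unreadable, although the 1-3 month TOE is required. The formula also gives completers and early leavers the same chance of an image. Subjects who leave before the 1-3 month visit have no image from it and are not completers, so for a given overall share imaged the downward error would be smaller than shown.
- At the procedure, TOE or ICE is required, so the missing-image effect is likely smaller there. It has not been quantified.

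**Conclusion.** The point holds as a defect of the stated rule. Taken literally, Section 12 applies a 2-year-completer denominator to a reading made at the procedure and at 1-3 months. It counts unimaged completers as not closed, treats early exits with leaks differently from early exits with closure, and gives the grades no common base.

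The size cannot be known from the protocol. Under assumed true closure of 90%, 85% retention and exit unrelated to grade or imaging, reported 1-3 month closure is 91.4% with complete imaging, 87.4% with 95% readable and 79.3% with 85% readable.

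Two stronger readings should be avoided. Imaged leaks with early exit do not disappear from the report, because they still count in their own grade. Nor do the grades always fail to sum to 100%: this needs early exit or missing images, and the two errors partly cancel. The correction is worth making, but it affects a descriptive result and not the study's objectives.

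**What to change.** In Section 12, limit the 2-year-completer denominator to events counted through 2 years, and add for closure:

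*Residual flow at the procedure and at 1-3 months will be reported as the number of subjects in each grade divided by the number of implanted subjects with a core-lab-readable image at that time point, regardless of later follow-up. The number not imaged or not readable will be shown alongside.*

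The cost is a sentence or two in the protocol, carried into the statistical analysis plan. No new data are needed.

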#### **4.2.2 Number of study subjects**

Approximately 1000 subjects will be enrolled in the study at up to 75 sites in EMEA, ANZ, Latin America, and AP. A list of clinical investigation sites and ECs will be kept under separate cover and is available upon request (**Appendix F**).

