## **4.3 Objectives**

### **4.3.1 Primary objectives**

The Amulet observational post-market study has four primary objectives:

1. Assessment of acute (0 - 7 days post procedure) serious adverse events
2. Assessment of late (> 7 days post-procedure) serious adverse events through 2 years
3. Report the percentage of stroke (ischemic), systemic embolism, and cardiovascular death through 2 years
  - Cardiovascular death is defined as (see **Appendix L**) death due to proximate cardiac cause, death caused by non-coronary, non CNS vascular conditions, death from vascular CNS causes, hemorrhagic stroke, ischemic stroke, all procedure related deaths, sudden or unwitnessed death and death of an unknown cause

4. Report the percentage of bleeding events through 2 years

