## **6.8 Subject Withdrawal**

Subjects must be informed about their right to withdraw from the study at any time and for any reason without sanction, penalty, or loss of benefits to which the subject is otherwise entitled. Withdrawal from the study will not jeopardize their future medical care or relationship with the investigator. Subjects will be asked to specify the reason for their termination, but have the right not to answer.

The investigator may decide to withdraw a subject from the study at any time with reasonable rationale. The subject's future care will not be influenced by a decision, voluntary or otherwise, to withdraw from the study. All reasonable efforts should be made to retain the subject in the study until completion of the study.

Reasons for subject withdrawal include, but are not limited to:

- Subject withdraws consent
- Subject refuses to continue their participation
- Subject does not meet the inclusion/exclusion criteria (withdraw attempt to treat subjects 7 days after the date of the attempted procedure)
- Subject is deceased (event or symptoms pertaining to outcome of death must be documented on an Adverse Event eCRF)
- Subject's participation is terminated by the PI or investigator, although the subject consented, since participation is no longer medically appropriate
- Subject is 'lost to follow up' (subject does not adhere to the scheduled follow up visits but has not explicitly requested to be withdrawn from the study)
- Site personnel should make reasonable efforts to locate and communicate with the subject in order to achieve subject compliance to the scheduled follow up visits

If a subject withdraws from the study, the site will record the subject's reasons for withdrawal on the Withdrawal eCRF.

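### One denominator for all rates, subjects with the event plus 2-year completers, drops event-free subjects who leave early and so tends to overstate the three 2-year primary rates and the acute rate

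*Protocol*

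**What the plan says.** Protocol Section 12 defines both halves of every rate. Numerator: "The numerator for all rates will be the number of subjects who experience the corresponding event". Denominator: "The denominator for all rates will be subjects who experience the corresponding event plus all other subjects who achieve 2-years of follow-up". The numerator carries no completion requirement. No other handling of incomplete follow-up is stated, and no rate is exempted.

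These rates are the study's main output. Section 12 says "No formal hypothesis will be tested for this observational post-market study", but that "point estimates and exact 95% confidence intervals will be provided for the following rates in the study". The list covers all four primary objectives in Section 4.3.1. Three run through two years: late serious adverse events (SAEs), bleeding, and the third objective, "Report the percentage of stroke (ischemic), systemic embolism, and cardiovascular death through 2 years". The first is short-term: "Assessment of acute (0 - 7 days post procedure) serious adverse events". On size, Section 4.2.2 says only "Approximately 1000 subjects will be enrolled in the study at up to 75 sites", with no expected event, death or dropout rates.

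Three other places decide who reaches two years and who has had an event:
- Section 6.8 lists death as a reason for withdrawal: "Subject is deceased (event or symptoms pertaining to outcome of death must be documented on an Adverse Event eCRF".
- Sections 8.1 and 8.1.3 make death itself an SAE. Appendix L counts cardiovascular, procedure-related and unknown-cause deaths as cardiovascular.
- Sections 6.1 and 6.8 withdraw subjects found ineligible during an attempted implant seven days after the attempt. Under Section 4.5 they are already enrolled.

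**The concern.** Whether a subject is analysed depends on the subject's own result. Someone with an event in month 1 who is lost in month 2 counts in full; someone followed event-free for 20 months and then lost counts for nothing.

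Two of the dropped groups have a fully known status. A subject who dies without the event did not have it within two years. A subject event-free through the acute window has a settled acute outcome, whatever happens later. Dropping either group discards information and raises the rate.

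Since the study tests nothing, these estimates and intervals are what it delivers. Each would depend partly on retention, and the exact interval would be placed around the shifted value. The protocol itself fixes the rule, so an analysis plan could correct it only by contradicting the protocol.

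**Working it through.** There is no stated power, precision or rate in the protocol to reproduce. All event, death and loss figures below are assumptions; only N = 1000 comes from the protocol.

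**1. Algebra.** Let E be subjects with the event, C event-free subjects reaching two years, D event-free subjects who do not, and N = E + C + D. The rule gives E/(E + C) = E/(N − D), which exceeds E/N by the factor N/(N − D) whenever D > 0.

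**2. Acute rate.** Assume 50 acute events in 1000, so 950 event-free, of whom a fraction later misses two years.

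| Event-free subjects leaving later | Rule | All enrolled |
|---|---|---|
| 5% | 50/952 = 5.25% | 5.00% |
| 10% | 50/905 = 5.52% | 5.00% |
| 20% (190 leave, 760 stay) | 50/810 = 6.17% (exact 95% CI 4.62-8.06) | 5.00% (3.73-6.54) |
| 30% | 50/715 = 6.99% | 5.00% |

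**3. Who is dropped, by 2-year endpoint.**
- Late SAE: withdrawals and losses without a late SAE. A death after day 7 is itself an event. Only a death inside the first seven days lies outside this endpoint.
- Objective 3: withdrawals and losses, plus non-cardiovascular deaths without prior ischemic stroke or systemic embolism.
- Bleeding: withdrawals and losses, plus all deaths without bleeding.

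**4. Size where death competes (objective 3, bleeding).** Constant yearly hazards: e for the event, d for death outside the endpoint, c for loss; L = e + d + c.
- Observed events: E/N = (e/L)(1 − exp(−2L)).
- Event-free completers: C/N = exp(−2L).
- Rule: E/(E + C).
- True 2-year cumulative incidence: e/(e + d) × (1 − exp(−2(e + d))).

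| e, d, c per year | E per 1000 | C per 1000 | Rule | True | Ratio |
|---|---|---|---|---|---|
| 2.5%, 4%, 2% | 46.0 | 843.7 | 5.17% | 4.69% | 1.10 |
| 2.5%, 8%, 5% | 43.0 | 733.5 | 5.54% | 4.51% | 1.23 |
| 2.5%, 10%, 8% | 41.0 | 663.7 | 5.82% | 4.42% | 1.32 |
| 6%, 4%, 2% | 106.7 | 786.6 | 11.94% | 10.88% | 1.10 |
| 6%, 10%, 8% | 95.3 | 618.8 | 13.35% | 10.27% | 1.30 |

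**5. Size with loss only (late SAE).** Same formulas with d = 0.

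| e, c per year | Rule | True | Ratio |
|---|---|---|---|
| 2.5%, 2% | 4.97% | 4.88% | 1.02 |
| 2.5%, 8% | 5.27% | 4.88% | 1.08 |
| 30%, 2% | 45.67% | 45.12% | 1.01 |
| 30%, 8% | 47.33% | 45.12% | 1.05 |

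**6. When the direction could change.** Steps 4 and 5 assume loss unrelated to event risk. Suppose 50 events are seen and 190 event-free subjects are lost, so the rule reports 6.17%. It is right if those 190 had unseen events at a rate q with (50 + 190q)/1000 = 0.0617, so q = 6.2%. Above that the rule understates. This applies only to losses: subjects who died without the event have no unseen events.

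**7. Technical success.** Assume 990 of 1000 subjects are implanted and the other ten are withdrawn at day 7. Read literally, the rule gives 990/990 = 100% instead of 990/1000 = 99.0%.

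**The case against.** The strongest defence is that this is a descriptive registry. No hypothesis, threshold or comparator depends on the rates, and for harms the likely error makes the device look worse. In the mild case the shift is about half a percentage point (5.17% against 4.69%). This limits the consequences but does not make the estimates right, and they are the primary results. Nor is the rule uniformly cautious: step 7 shows that it can flatter technical success.

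It is also fair that Section 12 says procedural SAEs will be summarised for all subjects, which suggests that the acute rate was not meant to require two years of follow-up. But the denominator sentence makes no exception, so the text must be reconciled.

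Three stronger readings are tempting and not supported:
- A reader might infer that all four primary rates are 2-year rates. Section 4.3.1 sets three; the fourth is acute and is affected only through the words covering all rates.
- A reader might infer that every death without the endpoint of interest is dropped everywhere, and so apply 10-32% to all rates. Deaths after day 7 are late SAEs, and objective 3 loses only deaths classed as non-cardiovascular. The protocol does not show that these alone would reach 4-10% per year.
- A reader might infer that the bias is always upward. That is certain against events over enrolled subjects, but not against cumulative incidence. With telephone contact at 6 and 24 months, unseen events among lost subjects are plausible.

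**Conclusion.** The rule is wrong as written and should be replaced. It conditions inclusion on the outcome for the three 2-year primary rates and, read as stated, for the acute rate. Overstatement against events over enrolled subjects follows from the algebra whenever event-free subjects leave. Against cumulative incidence it holds unless lost subjects have a clearly higher event risk than those retained.

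The size cannot be fixed from the protocol. With constant hazards, loss of 2-8% per year unrelated to risk and competing death of 4-10% per year, it is about 10-32% relative for event hazards of 2.5-6% per year. With loss only, as for late SAEs, it is about 1-8% for event hazards of 2.5-30% per year. The acute illustration of 5.00% becoming 6.17% needs no assumption about unseen events, provided that the acute status of the later leavers is known.

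**What to change.** Replace the denominator sentence in Section 12 with two rules.

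- **Acute, technical-success and procedural-success rates:** use all enrolled subjects as the denominator, with exact 95% intervals for the acute rate as planned.
- **2-year rates:** use all enrolled subjects and report cumulative incidence at two years from time to first event, censored at last contact, with 95% intervals. Treat death outside the endpoint as a competing event: Aalen-Johansen for objective 3 and bleeding. For late SAEs use 1 minus Kaplan-Meier, since death after day 7 is an event, and say how any death in the first seven days is handled.

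The present proportion may stay as a supportive table. The text should also say how the 24-month contact window of plus or minus 12 weeks relates to two years of follow-up, since a subject may properly have the last contact before 24 months.

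The cost is about one paragraph. The 2-year intervals will no longer be exact binomial. Event and last-contact dates must be available: adverse event, death, withdrawal and follow-up forms are listed in Section 6, but their contents are under separate cover, so this has to be confirmed.
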